### **Randomization**

The random allocation of patients to intervention vs. control groups will be conducted following enrollment in the trial (i.e., admission to study settings). Allocation will be completed in a concealed manner by a research methodologist in the Calgary Institute for Population and Public Health at the University of Calgary, using a random number generator that will produce a randomization list organized in blocks of 6.

The list will be used to prepare sealed, opaque, allocation envelopes that will be stored in a secure documents cabinet in the clinical setting. The Research Nurse and Research Assistant will then access these envelopes in the secure storage area to determine patient allocation at the time of randomization.

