## **Methods**

### **Trial design**

A parallel two group randomized controlled clinical trial will be conducted to assess the use of ForeSite PT™ system on a pressure-related skin and tissue changes, with progression to pressure ulceration; interface pressure; and the perceptions of healthcare providers and patients to the ForeSite PT™ system. Eligible consenting inpatients will be randomly allocated to either have the ForeSite PT™ system and the LCD monitor turned on (intervention group), or have the ForeSite PT™ system and the LCD monitor turned off (control group) in a ratio of 1:1. Both groups will be included in the study up to a maximum of 7 days. Interface pressure and clinical outcomes will be measured at baseline (within 24 hours of admission) and on the last day of enrollment in the trial (within 24 hours prior to discharge, or on the seventh day (whichever comes first)). The perceptions of patients allocated to the intervention group, and the perceptions of healthcare providers each time a patient in their care is allocated to the intervention group, will be measured on the last day of enrollment in the trial or on the seventh day (whichever comes first).

Ethics ID number: REB13-0794

Study Title: Effectiveness of a pressure-sensing mattress system for reducing the risk of pressure ulcer formation by lowering interface pressure in vulnerable patient populations: Parallel-two-group randomized trial

PI: [name]

Version number/date: V2 01/04/2014

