## **Participants**

### ***Recruitment***

Identification of eligible inpatients will be facilitated by the charge nurse, the patient care manager, and nurses on their respective units, and by daily review of new admissions. After an eligible patient has been identified, the Research Nurse or the Research Assistant will ask him or her (or a substitute decision-maker, if not capable of consenting), if he or she would be interested in participating in a study to evaluate a pressure sensing technology that provides real-time feedback to healthcare providers. If the patient agrees to participate, he or she will be asked to provide informed consent. The Research Nurse will set up the ForeSite PT™ system, including placing the sensor overlay under the linen and mounting the LCD monitor to the headwall. The Research Nurse will ensure that the overlay and monitor are functioning properly on a daily basis, and will instruct housekeeping on sterilization practices of these device components.

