### **Sample size**

A total of 600 patients will be recruited from Unit 36, Unit 58, and the ICU will be enrolled in the trial, in order to randomize 300 patients to each of the intervention and control arms. Sample size estimates for the primary outcome indicate a need for 294 patients in each of the intervention and control arms. This is based on an estimated control group event rate of 30%, an intervention group rate of 20% (i.e., a 33% relative risk reduction), an alpha level of 0.05, and 80% power.

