### **Blinding**

The researchers, who will be involved in data analysis, including the Principle Investigator, Co-Investigators, and the Research Coordinator, will be blinded to treatment allocation. The Research Nurse and the Research Assistant will both be involved in participant recruitment, the randomization process, and data collection, and will not be blinded to treatment allocations. It will be impossible to blind

Ethics ID number: REB13-0794

Study Title: Effectiveness of a pressure-sensing mattress system for reducing the risk of pressure ulcer formation by lowering interface pressure in vulnerable patient populations: Parallel-two-group randomized trial

PI: [name]

Version number/date: V2 01/04/2014

289 participants and healthcare providers as they will be able to see if the LCD monitor that displays  
290 information about the patient's surface pressure on the bed is mounted to headwall.

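### One stated block size of 6, with unblinded recruiters who also open the envelopes, makes about a quarter of allocations deducible and weakens concealment

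*Protocol*

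**What the plan says.** All references are to the protocol.

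- **Randomization.** One block size is given: "a randomization list organized in blocks of 6". The section also states safeguards: "Allocation will be completed in a concealed manner by a research methodologist" at the university, and "sealed, opaque, allocation envelopes that will be stored in a secure documents cabinet in the clinical setting". Allocation follows enrollment, which the section equates with admission to the study settings.
- **Who opens the envelopes (Randomization).** "The Research Nurse and Research Assistant will then access these envelopes in the secure storage area to determine patient allocation".
- **Who approaches patients (Recruitment).** Once an eligible patient has been identified, "the Research Nurse or the Research Assistant will ask him or her" about taking part. Identification comes from the charge nurse, the patient care manager and unit nurses, and from a daily review of new admissions.
- **Blinding.** The same two roles "will both be involved in participant recruitment, the randomization process, and data collection, and will not be blinded to treatment allocations".
- **Ratio and size.** Trial design sets 1:1 allocation. Sample size plans 600 patients "in order to randomize 300 patients to each of the intervention and control arms".

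The protocol does not say whether one list serves all units or each unit has its own. It also does not say whether the recruiting staff are told the block size.

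**The concern.** Sealed opaque envelopes stop anyone reading an allocation. They do not stop anyone deducing it from earlier ones. In a permuted block of known size, once three patients have gone to one arm, the rest of the block is settled, and the last place in every block is always settled. Prediction needs the block size and the past sequence. The block size is printed in the protocol, and the past sequence is visible to the two roles who open the envelopes and work unblinded.

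Those roles also decide, within limits, whom to approach and when. Some eligibility criteria leave room for judgment: expected stay on the unit, need for help with bed mobility, and whether repositioning would harm care. A recruiter who expects a particular arm next could, without intending it, bring forward or hold back a patient of higher or lower risk. The arms would then differ in patient risk from the start. Body habitus and mobility plausibly influence interface pressure, so the sensor-measured primary outcome could be affected as well as the skin composite.

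**Working it through.** **Inputs.** Block size 6 (Randomization), ratio 1:1 (Trial design), 600 patients (Sample size). Each block is therefore 3 + 3, and 600 / 6 = 100 blocks if there is one list. Assumption, not stated in the protocol: the observer knows the block size and sees every earlier allocation on the list.

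**The plan's own figure.** The protocol gives no figure for predictability. Its one derived figure, 294 per arm, reproduces with a two-sided 0.05 test, 80% power, rates of 30% and 20%, and no continuity correction:
[1.96 × √(2 × 0.25 × 0.75) + 0.842 × √(0.30 × 0.70 + 0.20 × 0.80)]² / 0.10² ≈ 293.2, rounded up to 294. Neither the point nor the fix changes it.

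**Allocations known with certainty.** An allocation is forced once the other arm has used its three places, so the number forced equals the length of the run of identical allocations that ends the block. There are C(6,3) = 20 equally likely sequences:

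| Final run | Sequences | Forced allocations |
|---|---|---|
| 1 | 2 × C(4,2) = 12 | 12 × 1 = 12 |
| 2 | 2 × C(3,1) = 6 | 6 × 2 = 12 |
| 3 | 2 × 1 = 2 | 2 × 3 = 6 |
| Total | 20 | 30 |

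Mean forced per block = 30 / 20 = 1.5. As a share, 1.5 / 6 = 25%, and over 100 blocks 100 × 1.5 = 150 of 600.

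**Best guess.** The observer always guesses the arm with more places left and tosses a coin when they are equal. Expected correct guesses in a block of 2k are k + ½ × [2^(2k) / C(2k,k) − 1]. For k = 3: 3 + ½ × (64/20 − 1) = 3 + 1.1 = 4.1. That is 4.1 / 6 = 68.3%, about 410 of 600, against 50% by chance. Among the allocations that are not forced, the hit rate is (4.1 − 1.5) / (6 − 1.5) = 2.6 / 4.5 = 58%.

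**Effect of varying the block size.** The example mix is 4, 6 and 8, each equally likely. This is an assumption for illustration.

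- Best guess: the same formula gives 2.83, 4.10 and 5.33 correct for sizes 4, 6 and 8, so (2.83 + 4.10 + 5.33) / 18 = 68.1%. The strategy needs only the running imbalance between arms, so hiding the block size does not defeat it.
- Certainty: in 300 simulated lists of 600, with an observer who knows the set of sizes but not the boundaries, 2.3% of allocations were certain (0.023 × 600, about 14). Mixing only 4 and 6 gave 5.4% certain and a best guess of 69%.

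Varying the block size therefore removes most of the certain predictions and almost none of the guessing advantage.

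**The case against.** The strongest reply is that the protocol does describe concealment: a list generated off the unit by a methodologist, sealed opaque envelopes, a secure cabinet, and allocation after enrollment. Even on the assumptions above, 75% of allocations are not determined in advance. Knowledge of the block size by the recruiters is an inference, since the protocol neither tells them nor keeps it from them. If one list runs across several units, tracking it means following allocations in all of them. Candidates are flagged by unit staff and by review of admissions, so recruiters do not choose freely from an open pool.

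Most of this stands, and it limits the point. A reader might infer that concealment fails outright; the stated safeguards do not support that. It does not remove the point, because those safeguards guard against reading the envelope, while the weakness is deduction from envelopes already opened. Allocation after enrollment does not help where the choice is made earlier, at the approach. Tracking is also realistic for two roles who open the envelopes themselves.

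Three other readings go too far:

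- **That the 68% hit rate comes from the fixed, stated size.** It hardly changes under mixed sizes. Only the 25% certainty depends on the size being known.
- **That the harm lies in subjective skin assessment.** The primary outcome is recorded by a sensor and the skin composite is secondary. Unblinded skin assessment is a separate matter that block size does not touch.
- **That analysis can do nothing about it.** Braden score, skin status, BMI, bed mobility and comorbidity are collected at baseline, and adjusted logistic regression is planned if notable differences appear. Measured imbalance can be partly handled; selection on unmeasured features cannot.

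**Conclusion.** The point holds as a weakening of concealment. A single block size printed in the protocol, combined with unblinded staff who both recruit and open the envelopes, makes an average of 25% of allocations (about 150 of 600) deducible in advance. This is conditional on those staff knowing or inferring the size and following the sequence of a list. The percentage applies to any list tracked in this way, apart from an incomplete last block; the count of 150 uses the planned 600.

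The calculation measures the opportunity for selection. It does not show that selection would occur, and the documents give no basis for estimating a resulting bias in the treatment effect. The change is worth making because it is cheap and leaves the sample size alone.

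**What to change.** 1. Have the methodologist regenerate the list with randomly varying block sizes, for example 4, 6 and 8. Remove the sizes from the protocol and keep them from recruiting staff. Certain predictions fall from 25% to about 2%.
2. State in the Randomization section that consent and baseline assessment are completed and logged irrevocably before allocation is revealed. Use sequentially numbered envelopes, opened in order, with the participant identifier and time written on each before opening. Numbering does not lower the 68% best-guess rate. It limits what can be done with a guess, because a patient cannot be dropped, delayed or swapped once logged, and it leaves an audit trail.

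Some guessing advantage remains at the moment of approach for as long as recruiters see past allocations, and the protocol should not claim otherwise.

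Cost: a new list, a short wording change, a small logging burden for each patient, and slightly less exact balance between arms at the end of recruitment. The 294 per arm is unchanged.

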### **Blinding**

The researchers, who will be involved in data analysis, including the Principle Investigator, Co-Investigators, and the Research Coordinator, will be blinded to treatment allocation. The Research Nurse and the Research Assistant will both be involved in participant recruitment, the randomization process, and data collection, and will not be blinded to treatment allocations. It will be impossible to blind

Ethics ID number: REB13-0794

Study Title: Effectiveness of a pressure-sensing mattress system for reducing the risk of pressure ulcer formation by lowering interface pressure in vulnerable patient populations: Parallel-two-group randomized trial

PI: [name]

Version number/date: V2 01/04/2014

289 participants and healthcare providers as they will be able to see if the LCD monitor that displays  
290 information about the patient's surface pressure on the bed is mounted to headwall.

## 291 **Analysis and Statistical Methods**

292 Subjects will be stratified by their pressure ulcer risk, as determined by their Braden Score.

293 Data analysis will involve use of Chi-square and/or Fisher exact tests for between-group (i.e.,  
294 intervention and control groups) comparisons of the primary outcome and the secondary outcomes, and  
295 the Wilcoxon rank sum test for between-group comparison of strategic shifting. Chi square and t-tests  
296 will be used to compare baseline characteristics between groups, and logistic regression will be used for  
297 adjusted analyses if there are notable between-group differences for important baseline characteristics.  
298 Correlation between pressure distribution (the study's primary endpoint) with the hard clinical outcome  
299 (pressure ulceration and pressure-related skin appearance changes) will also be explored.

300 Univariate statistics will be used to summarize changes in pressure distribution as per the interface  
301 pressure feedback provided by the ForeSite PT™ system.

302 Univariate statistics will be used to summarize close-ended survey data, while open-ended survey data  
303 will be thematically analyzed.

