## **Objectives**

The primary objective of this study is to:

1. establish the effectiveness of a pressure-sensing mattress system (ForeSite PT™ system) in its ability to reduce interface pressure as reflected in a composite of pressure measurements.

Ethics ID number: REB13-0794

Study Title: Effectiveness of a pressure-sensing mattress system for reducing the risk of pressure ulcer formation by lowering interface pressure in vulnerable patient populations: Parallel-two-group randomized trial

PI: [name]

Version number/date: V2 01/04/2014

The secondary objectives are to:

1. assess whether the ForeSite PT™ system reduces the incidence of pressure-related compromised skin and soft tissues, with potential for progression to overt pressure ulceration;
2. determine the minimum interface pressure that is associated with higher risk for pressure ulcer development through the correlation of clinical outcomes and pressure outcomes;
3. assess healthcare provider and patient perceptions of the ForeSite PT™ system; and
4. establish the cost-effectiveness of the ForeSite PT™ system.

Specifically, the study will address the following research questions:

1. Is the ForeSite PT™ system effective at reducing interface pressure by assisting healthcare providers in determining the best method for patient turning/repositioning?
2. Does the use of the ForeSite PT™ system reduce the incidence of pressure-related compromised skin and soft tissues, with potential for progression to overt pressure ulceration?
3. Does interface pressure correlate with clinical outcomes?
4. Does the ForeSite PT™ system have more impact on the clinical outcomes of patients who have been identified as having a higher risk of pressure ulceration as per the Braden scale?
5. What are the perceptions (both positive and negative) of healthcare providers to the ForeSite PT™ system with regards to functionality, ease of use, and interpretation of pressure data on the computer monitor?
6. What are the perceptions (both positive and negative) of patients (and if appropriate, family members) to the ForeSite PT™ system (including sensor pad and monitor display of their pressure points)?

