230 These questions were utilized in a prior pilot study assessing healthcare providers' perceptions to  
231 the interface pressure information provided on the LCD monitor, and the impact of this information  
232 on patient care. The survey will be administered to each healthcare provider once after their first  
233 use of the ForeSite PT™ system in the trial by the Research Nurse or the Research Assistant on the  
234 patient's last day of enrollment or on the seventh day (whichever comes first), and will take  
235 approximately 10 minutes to complete.

236

237 3. Perceptions (both positive and negative) of patients (and if appropriate, family members) allocated  
238 to the treatment group to the ForeSite PT™ system. This outcome will be measured by a survey  
239 consisting of seven close-ended and open-ended questions about prior experience with pressure  
240 mapping technology and the ForeSite PT™ system (including sensor overlay and monitor display of  
241 their pressure distribution) on their care and comfort. The survey will be administered by the  
242 Research Nurse or the Research Assistant, and will take approximately 10 minutes to complete.

243 In addition, a pressure ulcer risk assessment will be conducted, and demographic information and  
244 information on medical history will be collected from patient charts, to establish a patient profile at  
245 baseline, within 24 hours of admission, by the Research Nurse or the Research Assistant.

246 The Braden Scale will be administered to determine the patient's level of risk at pressure ulceration. The  
247 Braden Scale was developed to assist healthcare providers with assessing a patient's level of risk for  
248 pressure ulcer development and the course of a particular treatment. It is a summated rating scale  
249 composed of six subscales: sensory perception, activity, mobility, moisture, friction, and nutrition. Each  
250 subscale is scored from 1-3 or 1-4, for a total score that ranges from 6-23. A lower total score indicates a  
251 lower level of functioning and therefore a higher level of risk for pressure ulceration. Second, a head-to-  
252 toe skin assessment will be conducted for detection of pressure-related skin changes and for overt  
253 ulceration. It requires circling skin areas where the patient may have skin changes or a pressure ulcer,  
254 and labelling the same area with the numbers 1 to 9, which correspond with stages of skin change and  

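### Braden stratification is announced but used by neither the randomisation list nor the stated tests, and no stated method answers research question 4

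*Protocol*

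**What the plan says.** Five places in the Protocol bear on this point.

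- **Analysis and Statistical Methods** opens with "Subjects will be stratified by their pressure ulcer risk, as determined by their Braden Score". It gives no cut-off and no number of groups, and does not say whether allocation, testing or reporting is meant. It then names chi-square or Fisher tests between the two arms for primary and secondary outcomes, a Wilcoxon test for strategic shifting, and logistic regression for adjusted analyses, the last only when important baseline characteristics differ notably between arms. None of these is described as using Braden.
- **Randomization** has a methodologist "using a random number generator that will produce a randomization list organized in blocks of 6". No stratification factor is named, neither Braden nor unit. Allocation follows enrolment, which is equated with admission to the study settings.
- **Secondary Outcomes** places the Braden score at "baseline, within 24 hours of admission, by the Research Nurse or the Research Assistant", without tying it to the moment of allocation. The score is repeated at the end of follow-up. On the scale itself, each "subscale is scored from 1-3 or 1-4, for a total score that ranges from 6-23"; no risk threshold appears anywhere.
- **Objectives**, research question 4, asks whether the system has "more impact on the clinical outcomes of patients who have been identified as having a higher risk of pressure ulceration", as judged by the Braden scale.
- **Sample size** assumes 30% vs 20%, alpha 0.05 and 80% power, giving 294 per arm. Recruitment is planned at 300 per arm.

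**The concern.** Braden is given a role in one sentence, and nothing that follows carries it out. On either reading something is left open.

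- If allocation is meant to be stratified, the Randomization section does not provide for it.
- If the analysis is meant to be stratified, the same section announces strata, defines none, and lists tests that do not use them.

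Research question 4 makes this more than wording. It asks whether the treatment effect differs by risk, which is a comparison of two effects. A chi-square or Fisher test of arm against outcome, overall or within a risk group, does not make that comparison. The likely improvisation is to test within each Braden group and read a significant result in one and not in the other as a differential effect, which is unreliable.

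The stated rule for adjustment is also weak. Whether the model is adjusted, and for what, depends on which baseline differences are judged notable once the data are in. Braden and unit can be expected to predict skin outcomes whether or not the arms happen to differ on them. Adjusting only after an imbalance leaves the main model undetermined in advance and gives up precision when none is seen.

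**Working it through.** **1. The plan's own figure.** Inputs from Sample size: p1 = 0.30, p2 = 0.20, alpha 0.05 (two-sided assumed; sidedness is not stated), power 0.80, mean p = 0.25.

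n = [1.96·√(2·0.25·0.75) + 0.842·√(0.30·0.70 + 0.20·0.80)]² / 0.10² = (1.200 + 0.512)² / 0.01 ≈ 293.1, rounded up to **294**. This matches the Protocol. Power is 80.1% at 294 per arm and 80.9% at 300. The figure covers the overall comparison only and is not in question here.

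**2. Separate tests by Braden group.** This procedure is one possible meaning of the sentence; the Protocol does not state it. Assumptions: two groups, and the same true effect of 30% vs 20% in both. Those rates belong to the primary outcome and are borrowed as an illustration, because no rates are given for the clinical outcomes that question 4 concerns.

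Power with m per arm = Φ{[0.10·√m − 1.200] / 0.608}.

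- Equal split, m = 150: Φ{(1.225 − 1.200)/0.608} = Φ(0.040) = **0.516**.
- 30:70 split, m = 90 and m = 210: 0.340 and 0.659.

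Chance that exactly one of the two tests is significant although the effects are identical:

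- Equal split: 2 × 0.516 × 0.484 = **0.50**.
- 30:70 split: 0.340 × 0.341 + 0.659 × 0.660 = 0.116 + 0.435 = **0.55**.

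**3. What a direct interaction test could detect at N = 600.** Wald test of the difference between two Braden groups in risk difference (RD) or log odds ratio, two-sided 0.05. In both scenarios the effect is 15 points in the higher-risk group and 5 in the lower, a 10-point interaction. Rates and splits are assumptions.

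| Higher-risk group | Lower-risk group | Split | Power, RD | Power, log odds |
|---|---|---|---|---|
| 30% to 15% | 30% to 25% | 50:50 | 30% | 37% |
| 30% to 15% | 30% to 25% | 30:70 | 27% | 31% |
| 40% to 25% | 20% to 15% | 50:50 | 30% | 14% |
| 40% to 25% | 20% to 15% | 30:70 | 25% | 13% |

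First row on the RD scale: variance = (0.21 + 0.1275 + 0.21 + 0.1875)/150 = 0.0049, SE = 0.070, z = 0.10/0.070 = 1.43, power = Φ(1.43 − 1.96) ≈ 0.30.

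For 80% power on the RD scale with an equal split, total N would be about 2,250 to 2,310. Only an extreme contrast (30% to 10% in one group, no effect in the other) reaches 78% to 91% at N = 600. These figures are for a two-group Braden split. Power with the continuous score depends on its distribution, which the Protocol does not give.

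**The case against.** Four objections deserve an answer.

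1. **The sections need not conflict.** A reader might infer that the Protocol contradicts itself on whether randomisation is stratified. The documents do not support that. The Braden sentence stands under analysis, research question 4 gives a reason for grouping there, and a stratified or subgroup analysis is compatible with an unstratified list. This stands: the sections are unreconciled, no more.
2. **Within-group testing is not stated.** The chi-square and Fisher tests are defined as comparing intervention with control, and nothing says they will be run by Braden group or that significance will be compared across groups. This also stands. The 50% figure shows what one reading would cost; it does not describe the plan.
3. **The interaction model can be left to the SAP, which is not shown.** Its absence alone would indeed be no finding. The point rests on what the Protocol does state: a stratification that no listed test uses, a pre-stated question that no listed test answers, and adjustment that depends on observed imbalance. Blinding of the analysts to allocation, as the Blinding section provides, softens the last of these, but the choice of model still follows the data.
4. **Stratified lists are not required.** A reader might infer that separate lists by unit and Braden group are needed because the settings differ in risk. The Protocol nowhere claims balance by unit, and chance imbalance under valid randomisation does not bias the comparison. Such lists are a design preference, and covariate adjustment deals with the matter.

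**Conclusion.** The point holds in limited form. The role of Braden is announced and left undefined, the stated tests do not use it, and none of them answers research question 4. The sample size and the validity of the randomisation are unaffected.

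The size is conditional. If the stratification sentence were carried out as separate tests by Braden group, a spurious one-significant, one-not pattern would arise in about 50% of trials with an equal split and about 55% with a 30:70 split. Both figures assume an identical 30% vs 20% effect in the two groups. A direct interaction test avoids that error but has only about 13% to 37% power for a 10-point interaction at 600 patients, under assumed rates and splits. Question 4 can therefore be estimated in this trial but hardly settled.

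**What to change.** 1. Replace the stratification sentence with a statement that Braden is an analysis factor and not a randomisation stratum. The blocked list can stay as it is.
2. Pre-specify the baseline Braden score and unit as covariates in the between-group logistic model for the binary outcomes, in place of adjustment triggered by observed imbalance. Name the baseline score explicitly, since Braden is measured twice.
3. Answer question 4 with one arm-by-continuous-Braden interaction term in that model, reported as an estimate with its confidence interval. The continuous score avoids choosing a cut-off. Note that the term measures effect modification on the odds-ratio scale.
4. Label question 4 exploratory, with the low power given as the reason, and state that no inference will be drawn from comparing significance between Braden groups.

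The cost is a few sentences in the Protocol and slightly more analysis work. Braden is already collected and no new list is needed. The one real price is an open admission that question 4 is underpowered.

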## 190 **Outcomes**

### 191 **Primary Outcome**

- 192 1. A composite of interface pressure measurements that reflect the distribution of interface pressure  
193 at predetermined time intervals. These measures include:
- 194 a. proportion of participants that have pressure readings greater than 40 mmHg;
  - 195 b. average interface pressure (excluding sensels with 0mmHg reading); and
  - 196 c. the absolute number of sensels with pressure readings greater than 40 mmHg.

197 The measurement of this outcome will be facilitated by the ForeSite PT™ system's sensor overlay that  
198 continuously collects pressure readings. The array of the sensor overlay is a capacitive sensor with a  
199 0.625" spatial resolution. There are 52 rows x 118 columns for 6,136 sensing points. The ForeSite PT™  
200 system's software continuously samples interface pressure at a rate of 1 Hz, which can then be  
201 extracted for analysis. The data file is in a proprietary binary format, and can be exported to TXT or CSV  
202 formats for import into a spreadsheet program for analysis. This will be achieved by the sampling of  
203 pressure readings at specified time intervals before and after turning/repositioning when the ForeSite  
204 PT™ system's LCD monitor is turned on, and when it is turned off.

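### The primary outcome joins a binary, a continuous and a count measure, but the stated test and the sample size fit only a binary one, and the protocol does not say which result decides the trial

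*Protocol*

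**What the plan says.** The Primary Outcome section of the protocol defines the outcome as "A composite of interface pressure measurements that reflect the distribution of interface pressure" and lists three parts:

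- (a) "proportion of participants that have pressure readings greater than 40 mmHg"
- (b) "average interface pressure (excluding sensels with 0mmHg reading", in mmHg
- (c) "the absolute number of sensels with pressure readings greater than 40 mmHg", on an overlay with 6,136 sensing points

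The Objectives section also bases the primary objective on a composite of pressure measurements.

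The Analysis and Statistical Methods section states: "Data analysis will involve use of Chi-square and/or Fisher exact tests for between-group", and the same sentence continues "intervention and control groups) comparisons of the primary outcome and the secondary outcomes, and". It then assigns "the Wilcoxon rank sum test for between-group comparison of strategic shifting". T-tests are named only for baseline characteristics. Logistic regression is named for adjusted analyses if the arms differ notably at baseline. Changes in pressure distribution are to be summarised with univariate statistics, with no between-group test attached. The same section refers to pressure distribution as the primary endpoint.

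The Sample size section gives 294 per arm for the primary outcome, with 300 per arm to be randomised. The basis is an event rate of 30% in control and 20% under intervention, alpha 0.05 and 80% power. The event is not named.

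**The concern.** Chi-square and Fisher tests compare categories. Part (a) is categorical for each patient, but parts (b) and (c) are not, and the protocol gives no threshold that would make them so. It also gives no rule that turns the three parts into one value per patient. Two of the three named primary measures are therefore assigned a test that cannot be applied to them as defined.

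The trial's main conclusion is at stake. The three parts could point in different directions: average pressure might fall while the share of patients with any high reading does not change. The protocol does not say which of these would count as a positive trial. Whoever later settles this, by choosing a component, a cut-off or a combining rule, settles the criterion for success.

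**Working it through.** **1. Match each primary measure to the stated methods.**

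| Measure | Scale per patient | Chi-square/Fisher | Logistic regression | Cut-off given |
|---|---|---|---|---|
| (a) any reading above 40 mmHg | binary | fits | fits | 40 mmHg |
| (b) average pressure | continuous (mmHg) | does not fit | does not fit | none |
| (c) sensels above 40 mmHg | count, 0 to 6,136 | does not fit | does not fit | none for the count |

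The two methods in the section that would suit (b) or (c) are assigned elsewhere. The Wilcoxon test goes to strategic shifting, which the Outcomes section does not list, and the t-test goes to baseline characteristics.

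**2. Reproduce the sample size.** Inputs from the Sample size section: p1 = 0.30, p2 = 0.20, alpha 0.05, power 0.80. Sidedness is not stated, so two-sided is assumed. With pooled variance and no continuity correction:

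n = [z(0.975) × √(2 × 0.25 × 0.75) + z(0.80) × √(0.30 × 0.70 + 0.20 × 0.80)]² / (0.30 − 0.20)²

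= [1.960 × 0.6124 + 0.8416 × 0.6083]² / 0.01 = (1.7122)² / 0.01 ≈ 293.2, rounded up to **294 per arm**.

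This matches the protocol exactly. Power is 80.1% at 294 per arm and 80.9% at 300. The calculation covers one binary comparison at one alpha. It contains no standard deviation or mean difference for (b), no rate or dispersion for (c), and no division of alpha.

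**3. What would follow if all three were tested.** The protocol does not describe this scenario. Suppose each measure had an appropriate test at two-sided 0.05 and success on any one were enough.

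- Independent statistics: 1 − 0.95³ = 0.143.
- Equally correlated normal statistics, by simulation:

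| Assumed pairwise correlation | 0 | 0.3 | 0.5 | 0.7 | 0.9 |
|---|---|---|---|---|---|
| Family-wise error | 14.3% | 13.6% | 12.5% | 10.9% | 8.4% |

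The documents give no correlation. All three measures come from the same overlay, and at any one reading (a) is met exactly when (c) is at least 1. Independence is therefore not credible, and 14.3% is the top of the range.

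**4. The same scenario with a Bonferroni split** (0.05/3 = 0.0167). The 30% versus 20% comparison would need 392 per arm. Its power at 300 per arm would be about 67%.

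**The case against.** The best defence is that the protocol intends a single binary primary comparison. The event rates, chi-square/Fisher and logistic regression all fit that, and (a) is binary. The univariate summaries of pressure distribution could then be the descriptive handling of (b) and (c). This reading is coherent, and it means the primary analysis is not shown to be impossible. But the protocol never states it. Objectives and Primary Outcome both describe a composite, the analysis section calls pressure distribution the primary endpoint, and the 30%/20% event is not tied to (a).

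A second defence is that a statistical analysis plan, not available here, may supply cut-offs, derivations and multiplicity rules. That is fair, and their absence alone is not the point. The point is that three statements inside the protocol disagree, so a later plan would have to override one of them.

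Third, the Blinding section keeps those who analyse the data unaware of allocation. This limits choosing a component by its treatment effect, so post-hoc selection should not be presumed. It does not tell the reader which component decides.

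A reader might also infer that the three measures cannot be merged at all. That goes too far: a met/not-met rule or summed ranks could combine them per patient. What can be said is that no rule is given.

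**Conclusion.** The point holds as an internal disagreement. The primary outcome has three parts on three scales, the stated test and adjusted model fit one of them, and the sample size plans for one unnamed event. The protocol does not fix which result decides the trial. The 294 per arm is arithmetically right for a single binary endpoint.

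The inflation of about 8% to 14% is conditional. It assumes three unadjusted tests, success on any one, and pairwise correlations between 0.9 and 0.

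Stronger readings are tempting but not supported:

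- **That the plan tests three measures at 0.05 each.** Alpha 0.05 appears only in the sample-size calculation, and separate tests are nowhere described.
- **That requiring all three would leave about 51% power (0.8³).** This assumes independence and 80% power for each part. The protocol gives no power, effect or variability for (b) or (c).
- **That 300 per arm would act like about 191 (300 × 2/π).** This assumes a median split of normally distributed data. The protocol proposes no such split, and 294 was already computed for a binary event.

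**What to change.** Name one primary measure, with its per-patient definition and sampling time, and align Objectives, Primary Outcome, Sample size and the analysis section with it.

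- **If it is the binary measure:** chi-square and 294 per arm stand, provided the 30%/20% event is stated to be that measure.
- **If it is average pressure or the sensel count:** use an analysis suited to that scale, preferably adjusted for baseline, and restate the sample-size basis. The protocol contains no standard deviation or dispersion from which to do so.

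In either case, analyse average pressure and sensel count with methods for continuous or count data, such as a baseline-adjusted model or the Wilcoxon test, and keep chi-square/Fisher for binary outcomes. Place the two non-primary measures below the primary, either in a fixed testing sequence or as secondary outcomes. If the sponsor prefers to keep all three as primary, a stated multiplicity rule and a revised sample size are needed.

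Cost: two measures lose primary status. With a binary primary the rest is a change of wording. A non-binary primary also needs a new power justification. The change should be made before allocation is revealed to the analysts.
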